### Secondary outcome

#### Arterial stiffness

Arterial stiffness will be assessed by carotid-femoral Pulse Wave Velocity (PWV), which is the current gold standard for non-invasive measurement of aortic arterial stiffness [39], and by radial Pulse Wave Analysis (PWA), which derives the augmentation of the central pulse waveform via measurement at the peripheral (radial) artery. Both measurements will be taken with SphygmoCor^TM^ CPV (AtCor Medical) which employs applanation tonometry to measure the shape and velocity of the pulse wave, with good repeatability and reproducibility [40].

To ensure accuracy and reproducibility, measurements will be taken in the morning after fasting blood samples. Participants will be provided with a standardized breakfast (breakfast cereal and/or muesli bars) and will be asked to abstain from tobacco and caffeine at least 4 hours before the measurement. PWV will be assessed by measuring carotid and femoral artery wave-forms sequentially over the common carotid and femoral arteries. Radial PWA will be used to estimate central pulse pressure and augmentation index. Both PWV and PWA measurements will be measured in duplicate. Validity of the measurements will be assessed as per the SphygmoCor manual [41], with an operator index of >80 indicating a good quality measurement for PWA and a standard error <10% of the PWV value indicating a good quality measurement for PWV. Where significant disagreements between the measurements exist, the measurement will be repeated until measurements within 10% of each other are obtained.

#### Urinary protein and albumin

24-hour urine samples (gold standard for measuring proteinuria and albuminuria) [42] will be used in this trial. Participants will be provided with bottles for collection and educated on correct collection procedure in accordance with standard protocol. Storage and processing of the urine samples will also be carried out according to standard protocol. Both participants and investigators will be blinded to the urinary results.

### Fluid status

Fluid status, a predictor of cardiac alterations such as left ventricular hypertrophy [3], will be indicated by bio-impedance spectroscopy (BIS). This will be assessed by the Body Composition Monitor (BCM) (Fresenius Medical Care, Germany), which determines total body and extracellular water by measuring electrical resistance across 50 frequencies using electrodes placed on the wrist & foot, (5 to 1000 kHz) [43,44]. BIS is a quick, non-invasive method to assess fluid status, validated against gold standard dilution methods [45]. The BCM has been shown to be an accurate indicator of fluid change when compared to body weight before and after dialysis sessions in haemodialysis patients [44]. Measurements will be performed in accordance with the manufacturer’s instructions [46]. Patients with stents or pacemakers will be excluded from this assessment. Participants and investigators will be blinded to the BIS results.

### Secondary outcome - xerostomia index (thirst)

Thirst will be measured by the Xerostomia Index (XI) [47-49]. The XI is a score summated a subjective 11 item questionnaire [47] measuring the severity of the symptoms of dry mouth across one of five responses (‘never’, scoring 1; ‘hardly ever’, 2; ‘occasionally’, 3; ‘fairly often’, 4; and ‘very often’, 5)’. Each individual’s responses will be scored and summated to give a single XI score [47].

### Secondary outcomes: serum metabolic markers

Serum blood samples will be stored for analysis of markers of inflammation (CRP), adiponectin (total and high molecular weight), markers of renin-angiotensin-aldosterone system stimulation (renin, aldosterone, angiotensin-converting-enzyme) and a marker of fluid overload (NT-proBNP) in addition to the standard tests taken in practice (e.g. full blood count and urea and electrolytes). Blood samples will be collected after overnight fast and drawn from a peripheral vein while participants are seated. Blood will be centrifuged within 30 minutes after blood collection. After separation, plasma will be transferred using a graduated plastic disposable pipette into color coded storage vials and placed in freezer storage boxes in a −80°C freezer. Additional serum will be stored for the analysis of novel risk factors in the future. Participants and investigators will be blinded to the serum outcomes.

### Adherence/dietary intake measures

A multi-method approach to measuring dietary sodium intake was chosen to employ both objective and self-reported methods, optimizing accuracy of dietary intake estimation, while minimizing participant burden [50]. The current gold standard for dietary sodium intake measurement is repeated 24-hour urinary sodium excretion [51,52]. Due to the increased participant burden involved in 24-hour urine collection, 24 hr collections (at baseline and all follow up points) will be supplemented with mid-stream urine collections occurring weekly in Phase 1 and at follow up points in Phase 2 (see Figure 2). Mid-stream urinary sodium has recently been demonstrated to have good agreement with 24-hour urinary sodium in CKD [53,54], and the collection of 24-hour samples concurrently with mid-stream samples will allow for further exploration of the agreement between these measures. Mid-stream urine samples will be analyzed for sodium, creatinine and albumin concentrations (Figure 3).

**Figure 3 F3:**
[figure not shown]
LowSALT CKD study data collection schedule.

In addition to objective measures, a diet history and food frequency questionnaire (FFQ) will be used to measure dietary intake. In the diet history method, information about what is consumed over an extended period of time is collected using open-ended questions [55]. This is considered an ideal method for capturing ‘usual intake’ over a specified period of time [56]. To minimize the time burden and participant recall bias, which typically limit the use of the diet history, this trial will use a self-administered diet history (Wollongong method [56]) with forms mailed to participants in advance and verified by a dietitian interview. The FFQ, which is designed specifically to quantify sodium intake [52], will also be mailed with the diet history. Participants will complete these forms at home and bring them to their appointment where information will be verified by the study dietitian using food models and visual prompts to quantify intakes. Dietary histories will be entered into FoodWorks 7 (Xyris Software, Version 7.0.2915) using the Nuttab 2010 database (for general unbranded foods and known recipes), AusBrands 2012 database (where specific brand is known) and AusFoods 2012 (for convenience or pre-prepared foods where recipe is unknown). The FFQ will be scored as per Charlton protocol [52].

The final method for measuring intake will be a daily checklist, used throughout the entire 6 weeks of Phase 1. This is designed to capture intake of foods likely to contribute to a high sodium intake (from unpublished data of CKD patients at the PAH, (Longitudinal Assessment of Multiple Discrete Atherosclerotic Risk factors in Kidney Disease (Landmark) Study, [name] et al.), as well as daily record of study medication. The information on this checklist will be verified for completeness and accuracy. Adherence to the study medication will also be measured by pill count at trial end. Medication changes will be recorded, with all efforts made to avoid change of anti-hypertensive medications during the six week trial.

### Phase 2

Phase 2 of the trial (observational arm to 6 months after baseline visit) aims to assess long-term changes in outcomes and adherence to a sodium-restricted diet, as well as establishing common barriers and enablers to achieving dietary sodium restriction in this group. In this phase, barriers and enablers to adherence will be measured via four self-administered questionnaires. Self-efficacy will be measured using the health-related general self-efficacy scale [57] and health-related locus of control using the Multidimensional Health Locus of Control [58]. Beliefs about dietary compliance scale (BDCS) [59] and attitudes to dietary recommendations scale (ADRS) (modified from [60]) will be assessed. Results from the locus of control and self-efficacy scales will be used to identify predictors of dietary adherence. Results from the beliefs about dietary compliance (BDSC) will be used to identify specific barriers and enablers to dietary adherence. Results from the attitudes to dietary recommendations (ADRS) will assist in identifying specific recommendations with which participants find it difficult to adhere.

Another outcome specific to Phase 2 is taste assessment of the five basic taste senses: salty, sweet, bitter, sour and umami. Evidence suggests that hedonic liking and taste sensitivity of salty taste can be modified with adherence to a low sodium diet [61], however this is yet to be established in the CKD population. A further gap in the literature is whether restriction of dietary sodium could affect the other four taste senses; (sweet, bitter, sour and umami). In accordance with the International Standards Organization method of investigating sensitivity of taste [62], participants will be presented with 2 ml solutions of substances which represent each of the five basic taste qualities (and which are found ubiquitously throughout the food supply) and asked to identify each taste as well as the strength of the taste on a 10-cm visual analogue scale. This enables assessment of ability to detect each taste and the degree of sensitivity, measured at baseline and phase 2 follow up visits (Figure 2).

CKD patients have been found to have significantly decreased quality of life (QoL) with QoL decreasing as GFR declines [63]. Hypertensive patients have also been found to have reduced QoL scores when compared with normotensives [63]. Restricted sodium intake may increase quality of life by reducing symptoms associated with fluid overload, such as sleep apnea and edema. Therefore, quality of life (QoL) will be assessed by the Short Form-36.

Overall, Phase 2 aims to translate the promising indications from basic science into clinical practice demonstrating the effect of dietary sodium on blood pressure, risk factors for CKD progression and cardiovascular disease.

### Statistical analysis

The primary outcome will be change in 24-hour SBP from matched pairs of study subjects (by cross-over design) from MSI to LSI. Prior data indicate that the mean response of matched pairs is a 5 mm Hg change in BP with a standard deviation of 7 mm Hg (unpublished data from Todd et al. [64]). If the true difference in the mean response of matched pairs is 5 mmHg, 23 subjects across both treatments (to give 46 data sets) will be required to give a power of 90% with error of 0.05. Accounting for an adjustment factor of 1.56 (drop out of 20%; drop-in of 0%), a total of 37 patients will be recruited and pass run-in.

Analyses will be undertaken by analysis of covariance (ANCOVA) adjusting for baseline values using STATA (Version 12 [65]). To test for time order effects, both the treatment and treatment order will be included in the model. If the treatment order is not found to be significant, treatment group will be left in the model. Probability values of <0.05 will be considered significant. Test for normality of the distribution of each variable will be performed separately for each treatment group.

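### The trial is sized on a within-patient difference, but the listed ANCOVA terms include nothing that carries the pairing

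*Protocol article*

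**What the plan says.** All of this stands in the Statistical analysis section of the protocol article.

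- **Endpoint:** "The primary outcome will be change in 24-hour SBP from matched pairs of study subjects (by cross-over design) from MSI to LSI".
- **Sizing assumption:** "mean response of matched pairs is a 5 mm Hg change in BP with a standard deviation of 7 mm Hg".
- **Sample size:** "23 subjects across both treatments (to give 46 data sets) will be required" "to give a power of 90% with error of 0.05".
- **Recruitment:** "Accounting for an adjustment factor of 1.56 (drop out of 20%; drop-in of 0%), a total of 37 patients will be recruited".
- **Model:** "Analyses will be undertaken by analysis of covariance (ANCOVA) adjusting for baseline values". To examine time order effects, "both the treatment and treatment order will be included in the model". The section adds a rule for what stays in the model if order is not significant.

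The endpoint and the sizing are paired. The terms named for the model are baseline, treatment and treatment order. No patient effect, random effect or repeated-measures structure is mentioned.

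**The concern.** Treatment can be a model term only if each patient contributes one row per intervention, so the listed model needs two rows per patient. That fits the 46 data sets, but not an outcome that is already one difference per patient. Something must then link a patient's two rows, and none of the listed terms does so fully. A single pre-randomisation baseline has the same value in both rows. It removes part of the between-patient variation and leaves the rest in the residual.

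The SD of 7 mmHg behind the 90% power is the SD of a within-patient difference. A model that leaves between-patient variation in the residual does not use that SD. The risk is a primary test with less power than planned and an interval that is too wide. The same would apply to any continuous secondary outcome analysed in this way.

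**Working it through.** **Inputs from the article.** Difference 5 mmHg; SD of paired differences 7 mmHg; 23 pairs; 90% power; error 0.05 (sidedness not stated, taken as two-sided); 37 recruited; 20% drop-out.

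**Inputs assumed.** The total SD of 24-hour SBP is not given, so it is varied. There is one baseline per patient, and baseline, period 1 and period 2 values are equally correlated.

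**1. Reproduce the sample size.** The normal approximation gives ((1.96 + 1.28) × 7/5)² = 20.6, so 21. The paired t-test (noncentral t) gives 89.1% at n = 22 and 90.5% at n = 23. The stated 23 is reproduced exactly, for a paired analysis.

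**2. What the listed terms do to the standard error.** Let r be the correlation between a patient's two residuals after baseline adjustment.
- True SE of the treatment difference: 7/√23 = 1.46.
- SE reported by a model with no patient term: 1.46/√(1 − r).
- Raw correlation for a total SD of S: ρ = 1 − 49/(2S²).
- After adjusting for one baseline: r = ρ/(1 + ρ), which cannot exceed 0.5.

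Example, S = 10: ρ = 1 − 49/200 = 0.755; r = 0.755/1.755 = 0.430; model SE = 1.46/√0.570 = 1.93. With 46 − 4 = 42 degrees of freedom t = 2.018, so power ≈ Φ((5 − 2.018 × 1.93)/1.46) = Φ(0.75) ≈ 77%.

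**3. Simulation of the listed model** (ordinary least squares with treatment, order and baseline, no patient term; 6,000 trials per row for power, 3,000 under the null):

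| Assumed total SD | ρ | r | Power, 23 pairs | Type I error, 23 pairs | Power, 29 pairs |
|---|---|---|---|---|---|
| 5.2 | 0.094 | 0.086 | 90% | 4.8% | 96% |
| 6 | 0.319 | 0.242 | 87% | 2.8% | 94% |
| 7 | 0.500 | 0.333 | 83% | 2.1% | 92% |
| 8 | 0.617 | 0.382 | 81% | 1.4% | 90% |
| 10 | 0.755 | 0.430 | 77% | 1.5% | 88% |
| 12 | 0.830 | 0.454 | 76% | 1.2% | 87% |
| 15 | 0.891 | 0.471 | 74% | 1.2% | 86% |

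In the same data the paired analysis kept about 90% power at 23 pairs and about 96% at 29. At a total SD of 16 the listed model again gives about 74% at 23 pairs.

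**4. Interval width.** The ratio to the paired interval is 1/√(1 − r) × 2.018/2.074, with 42 against 22 degrees of freedom. At S = 7 (r = 0.333) this is 1.225 × 0.973 = 1.19. At S = 16 (ρ = 0.904, r = 0.475) it is 1.380 × 0.973 = 1.34. The interval is therefore about 20 to 35% too wide.

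**5. Completers.** 37 × 0.8 = 29.6, so about 29 pairs. This is the last column of the table.

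**6. The test of treatment order.** If order means sequence, it is a between-patient factor, and the same model rejects it about 9 to 11% of the time under no effect. If it means period, it is a within-patient factor, and the test rejects only about 1 to 2% of the time.

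**The case against.** The strongest objection is that independence of the two records is inferred, not stated. The section speaks of matched pairs and a cross-over design. The sentence on treatment and order explains how order is tested and need not list every term. ANCOVA does not exclude a subject factor, and a condensed article may leave the error structure to the full plan. This stands as far as it goes: a reader might infer that the trial will ignore the pairing and will not reach its 90% power, and the article does not establish either. It does not remove the point. The article goes beyond silence: it names a method, a covariate, two factors and a rule for keeping terms, and these do not match the paired sizing beside them. A single baseline and a sequence term are also collinear with fixed patient effects, so the listed terms do not point to that model.

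The size of the loss depends on an SD that the article does not give, and 37 recruits leave a margin over 23 pairs. Both objections stand and are reflected in the ranges. An SD near 5 mmHg, where the loss vanishes, would be tight for patients admitted with systolic pressures of 130 to 169 mmHg (Target population and eligibility criteria). Those are clinic readings, however, so this is only an orientation. The measurement schedule is in figures not shown, so the single baseline is also an assumption.

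A reader might also infer an inflated false-positive rate. For treatment the error is in the conservative direction. For treatment order, inflation follows only under the sequence reading, and the wording about time order allows period equally well. Under the sequence reading, order is also essentially orthogonal to treatment in complete pairs, so a false order signal would hardly move the treatment estimate.

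**Conclusion.** The point holds as a mismatch between a paired endpoint and sample size and a listed model with no term for the pairing. The sample size is not wrong, and in complete pairs the treatment estimate is unbiased under either analysis. The consequence is conditional on fitting the terms as listed, with one baseline per patient and a total SD of 7 to 16 mmHg. It is then a loss of roughly 7 to 16 percentage points of power at 23 pairs against the stated 90%. At 29 completers power runs from just above the 90% target to about 4 points below it. Because the error is conservative and the full plan may already contain a patient effect, this should be fixed but does not undermine the design.

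**What to change.** Replace the model sentence with one stating that 24-hour SBP, and each continuous secondary outcome, is analysed with treatment and period as fixed effects and patient as a fixed or random effect. For complete pairs, the equivalent is to compare within-patient MSI-LSI differences by sequence. Baseline may stay as a covariate if patient effects are random; with fixed patient effects a single baseline drops out. Say whether treatment order means period or sequence.

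The cost is one or two sentences. No new data are needed, the sample size is unchanged, and Stata 12 can fit the model. At 23 pairs this restores about 90% power.

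### No period term is named, and the order term meant to handle time effects appears to depend on a significance test, so a period shift can go unadjusted in the primary analysis

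*Protocol article*

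**What the plan says.** All of this stands in the Statistical analysis section of the Protocol article.

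- Outcome: "The primary outcome will be change in 24-hour SBP from matched pairs of study subjects (by cross-over design) from MSI to LSI".
- Model: "Analyses will be undertaken by analysis of covariance (ANCOVA) adjusting for baseline values using STATA".
- Time effects: "To test for time order effects, both the treatment and treatment order will be included in the model".
- Rule for the order term: "If the treatment order is not found to be significant, treatment group will be left in the model".
- Threshold: "Probability values of <0.05 will be considered significant".
- Sample size: "23 subjects across both treatments (to give 46 data sets) will be required to give a power of 90% with error of 0.05".

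No term called period is named. Nothing is said about what happens if order is significant. The Randomization section uses the word order for what is randomized, in blocks of 8, so treatment order most naturally means the sequence.

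**The concern.** In a two-period crossover, the time effect that matters for the treatment contrast is the difference between period 1 and period 2. Sequence is a different factor: it is constant within a patient and compares two groups of patients. If sequence is the only time-related term in a model of period-level data, the stated purpose and the stated term do not match.

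A period shift is plausible here. Diet education and food provision continue through Phase 1, and the low sodium diet is followed throughout (Dietary counseling, Table 1, Intervention). Period 1 therefore starts about one week into the diet and period 2 about four weeks in.

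The conditional rule is a second problem. It lets a test on the trial's own data choose the primary model, and it gives no path for one of the two results.

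The precision of the primary contrast is at stake. If completers are unequal between sequences, so is its centre.

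**Working it through.** **The plan's own figure.** The inputs are "the mean response of matched pairs is a 5 mm Hg change in BP with a standard deviation of 7 mm Hg", 90% power and alpha 0.05. Sidedness is not stated; two-sided reproduces the figure. A paired t-test (noncentral t) gives power 0.891 at n = 22 and 0.905 at n = 23, so 23 is confirmed. For dropout, 1/(0.8)² = 1.5625 and 23 × 1.56 = 35.9, or 36 against the stated 37. With 20% dropout, 37 × 0.8 = 29.6, so about 29 complete.

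**Which model is meant?**

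1. *Period-level data.* Treatment is a model term and 23 subjects give 46 data sets, which points to one row per patient and period. Sequence then cannot absorb a period shift, whether or not it is retained.
2. *Within-patient change.* This is how the outcome is defined. A centred order factor is then exactly the period adjustment, and the rule would remove it when non-significant.

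**Effect of leaving a shift unadjusted.** Let D be MSI minus LSI within a patient, with true mean 5 and SD 7. Let P be the shift from period 1 to period 2 (assumed). D has mean 5 + P when LSI comes first and 5 − P when MSI comes first. Without a period adjustment:

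- bias = P × (n LSI-first − n MSI-first)/N
- SD of D rises from 7 to about √(49 + P²): 7.3, 8.1 and 9.2 for P = 2, 4 and 6.

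Power comes from 100,000 simulated trials per scenario. The two ends of each range are the two directions of the shift relative to the larger sequence.

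| Completers | Shift (mmHg) | Bias (mmHg, either sign) | Power without period | Power with period |
|---|---|---|---|---|
| 12:11 | 2 | 2 × 1/23 = 0.09 | 0.88–0.90 | 0.90 |
| 12:11 | 4 | 4 × 1/23 = 0.17 | 0.81–0.87 | 0.90 |
| 12:11 | 6 | 6 × 1/23 = 0.26 | 0.68–0.79 | 0.90 |
| 15:14 | 4 | 4 × 1/29 = 0.14 | 0.91–0.94 | 0.96 |
| 15:14 | 6 | 6 × 1/29 = 0.21 | 0.82–0.89 | 0.96 |
| 17:12 | 4 | 4 × 5/29 = 0.69 | 0.82–0.97 | 0.95 |

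At 17:12 and 4 mmHg the estimate is 5.7 or 4.3 instead of 5.0. The 0.97 is not a gain, because it comes from the upward bias. With equal sequences the bias is zero.

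**How likely is 17:12?** Assume 4:4 blocks and dropout unrelated to sequence. Randomizing 37 gives at worst 20:17. After random loss to 29, the median imbalance is 1 patient, and 17:12 or worse occurs in about 14% of trials.

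**What the rule costs under reading 2.** At 12:11 the SE of the order coefficient is (7/2) × √(1/12 + 1/11) = 1.46, so a 4 mmHg shift lies 4/1.46 = 2.7 SEs from zero. By simulation, order is significant in about 26% of trials at 2 mmHg, 74% at 4 and 97% at 6. If order is kept whenever it is significant, which the text does not state, overall power stays at about 0.90 and the mean estimate within 0.05 mmHg of 5.0. The losses in the table therefore describe reading 1, or any trial in which the term is in fact dropped.

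**Cost of always keeping period.** With no shift, power at 23 pairs is 0.904 instead of 0.905.

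**The case against.** The wording is ambiguous, and this is a condensed article whose analysis plan is not shown; factor coding is commonly left to that plan. The outcome is defined as a within-patient change, for which order is a legitimate period adjustment. Treatment order might even be loose wording for first versus second period. The rule says only that treatment is left in the model, not outright that order is removed. In complete pairs under the period-level reading, removing sequence would not move the within-patient estimate. The run-in, the baseline ambulatory recording and the effort to hold antihypertensives and weight stable all work against a large shift, and 4 to 6 mmHg is about as large as the treatment effect itself. The inflation to 37 also buys margin: at 29 completers, 90% power survives a 4 mmHg shift.

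Most of this stands, and it limits the point. A reader might infer that the plan's primary estimate is biased, or that its model cannot handle a period effect at all. The document supports neither. Bias needs unequal completers, and the second inference holds only for the period-level reading. Splits far beyond 17:12 would need a bad start and nearly all dropout on one side. A figure for the power of a between-patient order test would need a between-patient variance that the document does not give, so none is offered.

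The objection does not rescue the text. The article does more than leave period to a later document: it names the term for time effects and gives a rule for it. Under the period-level reading that term does not do the job. Under the others, the rule apparently removes the term that does. What happens on a significant result is stated nowhere.

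**Conclusion.** The point holds in a limited form. The primary model does not clearly include period, and the term offered for time effects appears to hang on a p<0.05 test, so a period shift can be left unadjusted.

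The consequence is mainly lost precision. It is material at the 23 pairs on which the calculation rests if the shift is 4 mmHg or more, and modest at the 29 completers that the plan expects. Bias is negligible near balance and reaches about 0.7 mmHg, 14% of the 5 mmHg target, at 17:12 with a 4 mmHg shift. If order serves as the period adjustment and is kept when significant, the average cost of the rule is small; what remains is a primary model chosen on the trial data with one branch undefined.

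These sizes rest on the plan's SD of 7 mmHg, an assumed shift of 2 to 6 mmHg, and equal allocation within blocks.

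**What to change.** Replace the two sentences on treatment order. State that the primary analysis is within-patient (patient effects, or the paired difference with a centred order factor) and that treatment and period are retained whatever their p-values. Delete the rule that conditions the model on the order test, and report sequence or carry-over descriptively only, with no effect on which estimate is primary. If an analysis plan already says this, align the article's wording with it. Settle it before unblinding.

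The cost is two sentences and one degree of freedom. The sample size need not change.
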